### Treatments

Eligible patients will receive oral immediate-release morphine with a proportion of 10–20% daily total doses of oral morphine as the standard breakthrough pain treatment [24]. Patients will be instructed to use of study apparatus, which provides a fix concentration of nitrous oxide/oxygen mixture or oxygen to a disposable, demand valve, scented oral–nasal mask. Patients will hold the mask, which is opened by the negative pressure of patients to control the gas taken in. The experimental group will receive a fixed concentration of nitrous oxide/oxygen mixture and the control group will receive oxygen during breakthrough pain episodes. Gas inhalation will be administered until the breakthrough pain episode is over. The project manager is in charge of assignment, allocation, and treatment delivery. All gas cylinders used in both two groups are identical in appearance. The patients, nurse, and data collector are all blind to the treatment.

### Randomization, allocation concealment, and binding

Owing to the severity of the pain, ethicists suggest helping as many suffering patients as possible. In total, 240 participants will be randomized into four groups in a ratio of 3:1; three treatment groups (A, B, C), *n* = 180, and one control group (D), *n* = 60. The allocation sequence of each patient is decided by a computer-generated schedule, which is numbered by a statistician. The randomization schedule will be kept and sealed in an independent research room. Apart from the project manager, who is responsible for gas distribution, no other nurses or data collectors will have access to the data allocation. The nurse is blind to the double-blind randomized controlled trial lists (see Additional file 3) because the list does not indicate what treatment letters A, B, C, and D stand for.

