**Methods/design:**

This is a randomized, placebo-controlled, double-blind study; it will be conducted in the General Hospital of Ningxia Medical University. The target study subjects are at least 18 years old, and are hospitalized cancer patients who are receiving routine opioids to control cancer-related pain but still experience breakthrough pain. A total of 240 patients will be recruited and randomly allocated between three treatment groups (A, B, C) and a control group (group D) in a ratio of 3:1. All treatment groups (A, B, C) will receive standard pain treatment (oral immediate-release morphine) plus a pre-prepared nitrous oxide/oxygen mixture, and the control group (D) will receive the standard pain treatment plus oxygen. Patients, doctors, nurses, and data collectors are all blind to the experiment. Assessments will be taken before treatment (T0), at 5 min (T1) and 15 min (T2) during treatment, and at 5 min after treatment (T3). The primary endpoint measures will be the percentage of patients whose pain is relieved at T1, T2, and T3. Secondary outcome measures will include the safety of treatment, adverse events, and satisfaction from both health professionals and patients.

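### The letter code said to keep the nurse blind is decoded in the protocol itself, and the randomization section is inconsistent on whether she can see the list

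*Protocol article*

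**What the plan says.** All references are to the protocol article.

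- **Reason for the nurse's blindness** (Randomization, allocation concealment, and binding): she is blind to the lists, cited as Additional file 3, "because the list does not indicate what treatment letters A, B, C, and D stand for".
- **Meaning of the letters**: the same section names "one control group (D") and three treatment groups A, B and C. The abstract (Methods/design) describes patients as "randomly allocated between three treatment groups (A, B, C) and a control group (group D) in a ratio of 3:1" and adds that "the control group (D) will receive the standard pain treatment plus oxygen".
- **Access** (randomization section): "The randomization schedule will be kept and sealed in an independent research room", and, the project manager excepted, "no other nurses or data collectors will have access to the data allocation".
- **Roles** (Treatments): "The project manager is in charge of assignment, allocation, and treatment delivery".
- **Other safeguards** (Treatments): cylinders that look the same in both groups, and a scented mask.

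**The concern.** Masking by group letter works only while nobody who sees the letters knows what they mean. Here the meaning is printed in the protocol article, which was written before recruitment opened (Trial status gives a future start date). The reason offered for the nurse's blindness is therefore contradicted a few sentences away from where it is given.

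The outcomes are easily influenced. Pain relief is derived from a self-reported 0 to 10 score, and satisfaction is rated by patients and by healthcare professionals. Staff who know the arm could, without intending to, shape expectations or rate satisfaction accordingly. If recruiting staff could also see the sequence ahead of enrolment, they could influence who enters under D. Blinding lost in this way cannot be restored in the analysis.

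**Working it through.** **1. The letters against their published meaning.** The allocation figures are consistent: 240 × 3/4 = 180 active and 240 × 1/4 = 60 control, as stated. The list is said to withhold the meaning of A to D. The abstract gives it (A, B, C active; D oxygen), and so does the randomization section (A, B, C treatment; D control). A person with the list and the article can decode 240 of 240 patients.

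**2. The access statements side by side.** Two sentences say that the schedule is sealed and that, of the staff, only the project manager can reach the allocation. The next sentence says the nurse is blind because of what the list leaves out. If she never sees the list, its content is irrelevant to her blindness. The explanation makes sense only if she can see it. These statements need to be reconciled. Additional file 3 is not available here, so its content cannot settle the matter.

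**3. How much one broken letter reveals.** The article gives only the total of 180 for A, B and C. Assuming 60 in each:
- If D is identified, all 240 patients are decoded, because every other letter is then active.
- If one active letter is identified, 60/240 = 25% are decoded. The other 180 are 120 active and 60 control, so each is active with probability 120/180 = 67%.

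**4. How quickly outcomes could reveal D to someone who has not read the article.** Suppose an observer sees each patient's letter and has seen *k* patients per letter. With relief probabilities *p*ₜ (active) and *p*c (control), the probability that D has strictly the fewest responders is

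P = Σ over d of Bin(d; k, *p*c) × [P(Bin(k, *p*ₜ) > d)]³.

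For k = 3 at the 90% versus 10% of the sample size section:
- d = 0: 0.729 × 0.999³ = 0.7268
- d = 1: 0.243 × 0.972³ = 0.2232
- d = 2: 0.027 × 0.729³ = 0.0105
- d = 3: 0, since no active letter can exceed 3
- Sum: 0.960

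The same formula gives:

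| Relief, active vs control | Patients per letter | P(D uniquely lowest) |
|---|---|---|
| 90% vs 10% (protocol) | 3 | 0.960 |
| 90% vs 10% (protocol) | 5 | 0.995 |
| 80% vs 40% (assumed) | 3 | 0.560 |
| 80% vs 40% (assumed) | 10 | 0.899 |
| 70% vs 40% (assumed) | 5 | 0.550 |
| 70% vs 40% (assumed) | 20 | 0.914 |

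Only the first pair of rates is the protocol's. The others are assumptions that show the range.

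**5. Roles.** The project manager has access to the allocation and is in charge of assignment and of treatment delivery. Sealing the schedule against others does not separate these tasks.

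**The case against.** A reader might infer that allocation concealment and blinding fail outright. The documents do not support that, for these reasons:

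- Nurse access to the list is an inference from one sentence, and the two sentences before it deny such access. Nothing in the text shows that upcoming assignments are visible before enrolment.
- The blind does not rest on the letters alone. Sealing, restricted access, identical cylinders and a scented mask are also described.
- Nothing says the letter is printed on the cylinder or recorded beside the pain score. The probabilities above apply only to an observer who sees letters, pools outcomes by letter and has seen equal numbers of each. With smaller effects, few patients per letter reveal little (0.56 after 3 at 80% versus 40%).
- If the effect really were 90% versus 10%, staff could often guess the arm from the response under any labelling. Patient-level numbers prevent pooling across patients, but not that kind of guess.
- An unblinded person who distributes gas is not an error in itself. The project manager is not listed among the blinded, and nothing says that this person assesses outcomes. Nor does the article say who holds the letter-to-gas key.
- Labelling detail is commonly left to a full protocol.

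All of this stands, and it limits the point. It does not remove the core: the article chose to give a reason for the nurse's blindness, its own text defeats that reason, and its access statements conflict. That is something stated wrongly, not a detail left out.

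**Conclusion.** The point holds in a limited form. The letter code gives no protection against anyone who has both the list and the protocol, because the protocol publishes the key. The randomization section is inconsistent on whether the nurse can see the list. If she can, her blinding is compromised, and concealment may be too if the list shows assignments not yet made. If she cannot, the stated reason is simply wrong and the other safeguards carry the blind.

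Whatever the answer, four fixed letters are a fragile code: identifying D exposes all 240 allocations. The decoding probabilities (96% after 3 per letter at the protocol's rates, 90% after 10 at 80% versus 40%) depend on staff seeing each patient's letter, which the article neither states nor excludes. The overlap of allocation access, assignment and delivery in one role is an avoidable added risk.

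**What to change.** Before recruitment starts:

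1. Replace the group letters with a unique cylinder number for each patient that carries no group information. With no shared label, outcomes cannot be pooled by group, and one broken code exposes one patient.
2. Have the statistician hold the number-to-gas key, and not whoever assigns patients or delivers gas. Cylinders should be labelled from that key by a party outside the ward.
3. Release each number only after eligibility and consent are recorded.
4. Rewrite the randomization section so that it says nurses and data collectors see neither the list nor the key, and remove the explanation based on what the letters do not show.

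The cost is relabelling the cylinders, regenerating the list and slightly more labelling work. Sample size and power do not change. The minimum repair, if relabelling were refused, is to keep the letter key out of every document open to site staff and to state who can see the list. That corrects the contradiction but leaves the four-letter code as fragile as before.

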### Measurement

Patient’s demographic data (age, sex, nationality, height, weight), cancer diagnosis, baseline breakthrough pain intensity, current background pain opioid medication dosage, duration of nitrous oxide/oxygen mixture use, dosage of oral rescue morphine medication, and any side or adverse effects of nitrous oxide/oxygen mixture treatment will be recorded by researchers [45]. A numerical pain rating scale (range from 0 to 10) is used to assess for pain intensity along with heart rate, noninvasive monitoring of blood pressure, and digitally monitored oxygen saturation at baseline (T0 before treatment), 5 min (T1) and 15 min (T2) after the beginning of treatment, and at 5 min (T3) after treatment finished. Heart rate, blood pressure, and oxygen saturation will be monitored by Infinity® Delta XL (Draeger Medial Systems Inc., Danvers, Shanghai, China). A five-point satisfaction scale (5, very satisfied; 4, satisfied; 3, uncertain; 2, dissatisfied; 1, very dissatisfied) will be used to assess both patients’ and healthcare professionals’ satisfaction with breakthrough pain treatment [46]. Any side effects of the nitrous oxide/oxygen mixture treatment, such as nausea, vomiting, dizziness, drowsiness, and headache [17], will be carefully monitored by researchers after the initiation of the gases inhalation.

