**Fig. 1 Fig1:**
[figure not shown]
Study design framework. BP, blood pressure; BTP, breakthrough pain; HR, heart rate; NOOM, nitrous oxide/oxygen mixture: NRS, numerical pain rating scale; SPO_2_, oxygen saturation; STN, standard treatment with nitrous oxide/oxygen mixture; STO, standard treatment with oxygen

**Table 1 Tab1:** Schedule of enrolment, interventions, and assessments

	Study period				
	Enrolment	Post-allocation			Close-out
Timepoint	Diagnosed with breakthrough pain	Breakthrough pain episode (T0)	5 min after starting intervention (T1)	15 min after starting intervention (T2)	5 min after finishing intervention (T3)
Enrolment					
Eligibility screen	√				
Informed consent	√				
Allocation	√				
Interventions					
Control group			√	√	
Treatment groups			√	√	
Assessments					
Numerical pain rating scale		√	√	√	√
Blood pressure		√	√	√	√
Oxygen saturation		√	√	√	√
Heart rate		√	√	√	√
Satisfaction					√
Side effect			√	√	√

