### Participants

All cancer patients from the oncology ward who have breakthrough pain will be invited to participate. Davies’ Adapted Diagnostic Algorithm will be used to screen patients for the presence of breakthrough pain [8]. The main inclusion criteria are: Chinese-speaking patients older than 18 years; recent worst pain (breakthrough pain) reported to be 4 or higher on a numerical pain rating scale of 0 to 10; a score on the Karnofsky Performance Status Scale above 20; and ability to take deep breaths in order to use the self-administered device. Patients will be excluded if they have a known contraindication to the use of nitrous oxide or have impaired cognitive function. Specific inclusion and exclusion criteria are presented in Table 2.

**Table 2 Tab2:** Inclusion and exclusion criteria

Inclusion criteria
Patient aged 18 years or older
Patient experiencing breakthrough pain episode with a stable dose of opioids to control background pain
Written informed consent for participation obtained prior to any study procedures
Exclusion criteria
Patient with mental disorder, altered mental status
Patient has difficulty in reporting pain
Karnofsky Performance Status Scale score under 20
Abdominal distension or suspected bowel obstruction, air embolism, pneumothorax, decompression sickness, epilepsy, pulmonary cancer, chronic obstructive pulmonary disease and acute respiratory infection, pregnancy, severe inhalation injury; pharmaceutical or pathological pulmonary fibrosis; maxillofacial injuries
Disease involving ear, nose, larynges, such as sinuses, middle ear

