#### Secondary endpoint measures

Secondary outcome measures will include treatment safety, adverse events, and satisfaction from both health professionals and patients. The total time of nitrous oxide/oxygen mixture administration will be also recorded.

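### Side effects are recorded at T1, T2 and T3 but not at T0, so symptoms already present in opioid-treated cancer inpatients cannot be told apart from new ones

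*Protocol article*

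**What the plan says.** Two places in the protocol article fix when side effects are read, and they agree.

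- **Measurement.** Side effects, "such as nausea, vomiting, dizziness, drowsiness, and headache [17], will be carefully monitored by researchers after the initiation of the gases inhalation". The baseline reading covers the pain scale, heart rate, blood pressure and "digitally monitored oxygen saturation at baseline (T0 before treatment), 5 min (T1) and 15 min (T2) after the beginning of treatment". The other data listed for recording include no symptom taken before treatment. The same section states that "any side or adverse effects of nitrous oxide/oxygen mixture treatment will be recorded by researchers".
- **Table 1 (Study design).** The rows for pain scale, blood pressure, oxygen saturation and heart rate are ticked at T0, T1, T2 and T3. The side-effect row is blank at T0 and ticked at T1, T2 and T3.

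The abstract describes the population as "hospitalized cancer patients who are receiving routine opioids to control cancer-related pain but still experience breakthrough pain". Table 2 requires a "Patient experiencing breakthrough pain episode with a stable dose of opioids to control background pain". Under Treatments, every eligible patient also takes oral morphine for the episode. Under Secondary endpoint measures: "Secondary outcome measures will include treatment safety, adverse events, and satisfaction from both health professionals and patients".

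**The concern.** The five symptoms named in Measurement are non-specific. Cancer patients in hospital on regular opioids can plausibly have one or more of them before any gas is inhaled. A symptom seen at T1 may therefore have been there at T0 or may have started with the gas, and the schedule collects nothing that separates the two. The article shows no rule for doing so either. Data collectors are blind to treatment, so they cannot attribute a symptom by knowing which gas was given. If they informally leave out symptoms that were already there, no T0 record exists to check this.

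Two results are at stake, both secondary. One is the side-effect rate within the nitrous oxide groups, which readers will quote as the tolerability of the gas. The other is the comparison with oxygen, which has only 60 controls and so little precision to lose.

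**Working it through.** **Plan's own figure.** The article gives no expected side-effect rate, so there is none to reproduce on this point. Its one calculated size, 12 patients, concerns pain relief (90% v 10%, two-sided 0.05, power 90%). The pooled two-proportion formula at 1:1 returns it: 6 per arm, 12 in total. It has no bearing here.

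**Inputs from the article.** 180 patients in groups A, B and C, 60 in group D (Randomization section). Proportions are compared by chi-squared or Fisher's exact test (Data management and analysis).

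**Assumed inputs, for illustration only.** Share with any listed symptom at T0, persisting afterwards: b = 20% or 40%. New onset among the rest: t = 15% on nitrous oxide, c = 5% on oxygen. The five symptoms are treated as one any-symptom composite.

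**Formulas.**
- All symptoms counted: rate = b + (1 − b)r, with r = t or c.
- Only new symptoms counted, all patients in the denominator: rate = (1 − b)r.
- Difference in either case: (1 − b)(t − c).
- Pooled SE = √[p(1 − p)(1/180 + 1/60)], where p is the rate over all 240 patients; z = difference / SE.

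**All symptoms counted.**
- b = 20%: 0.20 + 0.80 × 0.15 = 32% v 0.20 + 0.80 × 0.05 = 24%. p = (57.6 + 14.4)/240 = 0.30; SE = √(0.21 × 0.02222) = 0.0683; z = 0.08/0.0683 = 1.17.
- b = 40%: 49% v 43%. p = (88.2 + 25.8)/240 = 0.475; SE = √(0.2494 × 0.02222) = 0.0744; z = 0.06/0.0744 = 0.81.

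**Only new symptoms counted.**
- b = 20%: 12% v 4%. p = (21.6 + 2.4)/240 = 0.10; SE = √(0.09 × 0.02222) = 0.0447; z = 0.08/0.0447 = 1.79.
- b = 40%: 9% v 3%. p = (16.2 + 1.8)/240 = 0.075; SE = √(0.0694 × 0.02222) = 0.0393; z = 0.06/0.0393 = 1.53.

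| T0 prevalence | All counted: rates, relative risk, z | New only: rates, relative risk, z | Share of nitrous oxide events present at T0, if all counted |
|---|---|---|---|
| 20% | 32% v 24%, 1.33, 1.17 | 12% v 4%, 3.0, 1.79 | 0.20/0.32 = 63% |
| 40% | 49% v 43%, 1.14, 0.81 | 9% v 3%, 3.0, 1.53 | 0.40/0.49 = 82% |

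On a denominator of all patients, the absolute difference is the same under both counts (8 or 6 points). What changes is the within-arm rate, the relative risk and the standard error.

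**Sensitivity to the assumed onset.** With 20% v 5% new onset and T0 prevalence of 10%, 30% and 50%, power is 56%, 29% and 18% when all symptoms are counted. It is 80%, 67% and 48% when new onset is counted among patients free of symptoms at T0. With no symptoms at T0 it would be 85%. The pattern is the same; the size moves with the assumptions.

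**The case against.** The strongest case against the point has five parts.

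1. **Counting rule.** A reader might infer that a patient already nauseated at T0 will be recorded as having a side effect of the gas. The article does not say so. It speaks of effects of the mixture, and staff may record only new symptoms. Event definitions are also commonly left to a fuller document. This stands, and it limits the point to what the schedule shows: old and new symptoms cannot be told apart. The missing T0 reading is not a detail left open, because the printed schedule and the text both start after exposure.
2. **Direction of the error.** A reader might infer that the gap hides the difference from oxygen or biases the comparison. Patients are randomized, so symptoms present at T0 are expected equally in all groups and create no false difference. The fair word is diluted. Randomization does not protect the within-arm rate.
3. **Significance.** With an unpooled standard error, the new-symptom z values are 2.3 and 2.0, and a reader might infer that the fix turns a non-significant result into a significant one. Under the planned chi-squared test they are 1.79 and 1.53, and neither passes 1.96. A gain in precision remains.
4. **Assumptions.** Prevalence, persistence and onset have no source in the article. The composite is not defined there, and the model gives no new event to a patient who has one symptom at T0 and later develops another. Reported symptom by symptom, T0 prevalence would be lower. The exclusions of altered mental status and suspected bowel obstruction in Table 2 may remove some drowsiness and nausea at T0. All of this stands, so the figures are an illustration and not an estimate.
5. **Basis of the 240.** A reader might infer that patient side effects determined the sample size. The Sample size section refers to feasibility and to the safety of nursing staff, so it does not support that. The importance of the point rests on safety and adverse events being named secondary outcomes.

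**Conclusion.** The point holds as a gap in the assessment schedule. Table 1 and the Measurement section both start side-effect recording after inhalation begins, so new symptoms cannot be separated from those already present, and no later analysis can recover the missing reading. If all symptoms present after the start are counted, within-arm rates are inflated and the contrast with oxygen is diluted, but not biased under no effect.

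The size is unknown, because the documents give no T0 prevalence. Under the assumptions shown, z is about 1.2 or 0.8 with all symptoms counted and about 1.8 or 1.5 with only new ones. The documents do not support the stronger readings that T0 symptoms are to be attributed to the gas or that a real difference would be concealed. The primary endpoint is unaffected. This is an inexpensive improvement to a secondary safety outcome.

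**What to change.** - In Table 1, tick the side-effect row at T0.
- In Measurement, have the same symptom list asked before the mask is applied.
- Define the side-effect outcome as a symptom new or worse than at T0, and report it by arm in all four groups.

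The cost is one short symptom check at a time point where pain score and vital signs are already taken, and one more column on the form. The T0 check does not establish that the gas caused a symptom. All patients also take morphine for the episode, so attribution still rests on the comparison with oxygen.
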